##### Parent guides

EJDeR is guided by a parent guide with documented advanced CBT skills. Parent guides attend a training workshop on (1) LICBT, (2) psychological and psychosocial concerns experienced by parents of persons treated for cancer during childhood, (3) basic knowledge about childhood cancer, for example, diagnoses and treatments, (4) the structure of EJDeR, and (5) telephone guidance protocols.^58^ A licensed psychologist with experience of the population and the external PAB coordinator with lived experience being a parent to a person treated for cancer during childhood deliver the training workshop. A licensed clinical psychologist or clinical expert in LICBT provides parent guides with weekly supervision (case management and clinical skills development),^59^ with additional at-need supervision provided if needed.

##### Telephone guidance

Guidance follows structured LICBT protocols.^60
61^ During the first week of the intervention, the parent guide schedules an initial assessment session (≈45 min) with the parent. The parent guide assesses the participant’s main psychological difficulties and provides the rationale (ie, how the techniques work) for behavioural activation and worry management. Working collaboratively with the participant they agree which LICBT technique to start working with. Participants work through the Introduction and Psychoeducation Module and begin working with the chosen LICBT technique, for example, by reading the workbook, listening to audio recordings of workbook text, and completing exercises. Thereafter, the parent guide provides up to 10 weekly telephone ‘check-in’ sessions (≈15 min) to the participant to review progress, problem-solve any difficulties experienced, and plan next steps. A relapse prevention session (≈30 min) is provided during week 12.

Sessions will be audio recorded (with consent) and we will select a random 15% of recorded sessions to examine parent guide fidelity to the EJDeR guidance protocols. The sampling strategy and fidelity assessment method are described in full in the process evaluation protocol.^53^ Guidance sessions can still take place if the participant does not consent to them being recorded. Parent guides will record data on intervention implementation and self-reported data from participants on intervention engagement in a session log and keep clinical notes to facilitate guidance.

An overview of the EJDeR intervention structure is provided in figure 3. Participants randomly assigned to EJDeR will be able to access usual care.

**Figure 3 F3:**
[figure not shown]
Structure of the EJDeR intervention.

##### Minimum treatment dose

The minimum treatment dose is defined as participants attending the initial assessment session with the parent guide and completing at least 4 weekly telephone guidance sessions with the parent guide. This is based on evidence suggesting a minimum of four LICBT guidance sessions are required to achieve an intervention effect.^62^

### Usual care

Participants can continue with usual care,^63^ which may include any type of care, for example, psychological support in accordance with national guidelines for treatment of depression and anxiety,^64^ and/or prescribed psychotropic drugs via primary care. Participants allocated to the control group will not be offered EJDeR at the end of the trial.

### Withdrawal

Without giving a reason, participants can contact the research team to withdraw from the trial and/or the intervention by contacting the research team via telephone or SMS or during a conversation with their parent guide. Participants in the intervention group may withdraw from the intervention but continue trial participation, for example, answer questionnaires and vice versa.

### Outcomes

#### Primary feasibility outcomes

Feasibility outcomes relate to procedural, intervention and methodological uncertainties following recommendations for designing and conducting pilot RCTs.^31
51^ We will follow a ‘GO-AMEND-STOP’ progression framework, with STOP indicating ‘do not progress to a future superiority RCT’, AMEND indicating ‘modifications needed to progress to a future superiority RCT’, and GO indicating ‘progress to a future superiority RCT’.^31^
Table 2 summarises feasibility outcomes and progression criteria indicating GO.

**Table 2 T2:** Feasibility outcomes and progression criteria indicating GO

Feasibility outcome	Progression criteria indicating GO	Rationale
Procedural uncertainties		
Proportion invited randomised	≥9.0%	Informed by the enrolment rate (11.0%) found in ENGAGE, with the percentage lowered to account for randomisation potentially leading to lower enrolment rates
Proportion completing all questionnaires at baseline, post-treatment (12 weeks), and follow-up (6 months post-treatment)	≥70.0%	Informed by progression criteria set for ENGAGE
Proportion of responses missing in each questionnaire at baseline, post-treatment (12 weeks), and follow-up (6 months post-treatment)	≤10.0%	Informed by research suggesting missing data ≥10.0% is considered substantial and statistical analysis is likely to be biased^76^
Intervention uncertainties		
Proportion completing the minimum treatment dose	≥65.0%	Informed by research suggesting an average 64.0% of participants adhere to guided web-based mental health interventions^77^

#### Clinical and health economic outcomes

We will collect clinical and health economic outcomes at baseline, post-treatment (12 weeks), and follow-up (6 months post-treatment) via telephone.

##### Primary clinical outcome

Mental well-being is measured with the Questionnaire on Well-Being (QWB).^65^ The QWB contains 18 items measuring subjective well-being and psychological functioning. It has excellent reliability, with Cronbach’s alpha between 0.93 and 0.94, and high test-retest reliability.^65^ Scores range from 0 to 72, with a higher score indicating better well-being.

##### Secondary clinical outcomes

Symptoms of depression are measured with the Patient Health Questionnaire 8-item scale (PHQ-8).^66^ Scores range from 0 to 24, with a higher score indicating higher depression severity.

Symptoms of anxiety are measured with the Generalised Anxiety Disorder 7-item scale (GAD-7).^33^ Scores range from 0 to 21, with a higher score indicating higher anxiety severity.

Post-traumatic stress symptoms are measured with the Post-traumatic Stress Disorder Checklist-Civilian version (PCL-C).^67^ Scores range from 17 to 85, with a higher score indicating higher PTSS severity.

##### Health economic outcomes

Health-related quality of life is measured with the 10-item Recovering Quality of Life (ReQoL-10).^68^ The ReQoL-10 contains 10 items assessing mental health-related quality of life and one item assessing physical health. Scores range from 0 to 44, with a higher score indicating better quality of life.

Societal resource use is measured with a Resource Use Questionnaire (RUQ),^69
70^ adapted by our research team in collaboration with the PAB. The RUQ includes questions from the Trimbos and Institute of Medical Technology Assessment Cost Questionnaire for Psychiatry^69^ and PECUNIA Resource Use Measurement Instrument.^70^ It covers healthcare utilisation (primary care visits, specialist visits, emergency department visits and other healthcare services), medication use, support groups, helplines, and absenteeism and presenteeism related to both paid and unpaid work, and personal expenses.

We will use a micro-costing approach to estimate the costs associated with delivering EJDeR, including time for initial assessment and weekly telephone sessions with parent guides, supervision, training, equipment, developing and producing workbooks, producing audio files, printing, distribution, and administration.

### Process outcomes

We will collect process outcomes at post-treatment (12 weeks) for the intervention group. Experience of the content and delivery of EJDeR is measured with the Theoretical Framework of Acceptability Questionnaire (TFAQ).^71^

Satisfaction with the relationship with the parent guide is measured with the Working Alliance Inventory – Short Revised (WAI-SR).^72
73^

We will conduct semi-structured interviews, described in a separate protocol paper for the embedded process evaluation.^53^

### Harms

We define harms as serious adverse events (SAEs), that is, any expected or unexpected adverse event, related, possibly related or unrelated to the EJDeR intervention or the trial, that results in death, a life-threatening adverse event or requires hospitalisation, which includes suicide attempts and self-harm. All SAEs are reported to the principal investigator ([name]).

We will assess SAEs through spontaneous reporting by participants to research team members or parent guides and ongoing monitoring by parent guides during intervention delivery.

A licensed psychologist will train research team members working with recruitment and data collection to identify signs of serious mental illness and/or risk of suicide. In acute situations, for example, where a participant discloses an immediate risk to their safety, research team members will contact emergency services regardless of the participant’s response. In non-acute situations, for example, suicidal ideation without immediate risk, we will inform the participant that we would like a licensed psychologist in our research team to contact them, and, if the parent gives permission, the licensed psychologist will contact them within two working days to conduct a risk assessment. If the participant does not give permission, they are encouraged to contact primary care. If a parent is assessed as needing more support than we can provide within the trial, we will direct them to appropriate mental health services and exclude them from the trial. If a parent guide identifies signs of serious mental illness (including deterioration) and/or risk of suicide, for example, when receiving telephone guidance from the parent guide, the parent guide will conduct the risk assessment immediately and consult with the parent guide supervisor if needed.

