### Intervention and control groups

We will randomly assign participants to EJDeR plus usual care (intervention group) or usual care alone (control group). We chose usual care as the comparator because this reflects current standard care in Sweden where only a minority of parents of persons treated for cancer during childhood receive psychological support after treatment completion; it allows us to assess the feasibility of delivering EJDeR in addition to usual care, and it informs the design of a future superiority RCT comparing EJDeR plus usual care versus usual care alone. Procedures for identifying and responding to participant deterioration or disclosure of risk during the trial are described under Harms.

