### Statistical methods

Quantitative data analysis is primarily descriptive and addresses outcomes related to procedural, intervention, and methodological uncertainties. Research team members will conduct the analysis following a pre-specified statistical analysis plan, with PAB members contributing to sense-making and interpretation of results. We will illustrate trial flow using a CONSORT diagram for pilot and feasibility studies.^51^

We will use independent samples t-test (continuous data) and χ² test (categorical data) to examine potential differences in sociodemographic characteristics between those invited versus those who consent.

We will calculate the proportion of those invited who consent, are assessed for inclusion, are included and are randomised, alongside 95% CIs. We will calculate the proportion of participants in the intervention and control group who complete questionnaires at baseline, post-treatment (12 weeks), and follow-up (6 months post-treatment), alongside 95% CIs. We will calculate the proportion of responses missing in each questionnaire for the intervention and control group at baseline, post-treatment (12 weeks), and follow-up (6 months post-treatment), alongside 95% CIs. We will calculate the proportion of the intervention group who complete the minimum treatment dose, alongside 95% CIs.

For clinical, health economic and process outcomes, we will report means and standard deviations (SDs) for normally distributed continuous variables, medians and interquartile ranges (IQRs) for non-normally distributed continuous variables, and frequency and percentages for categorical variables.

We will calculate the SD around the mean score on mental well-being (QWB) for the intervention and control group at post-treatment (12 weeks) and follow-up (6 months post-treatment) to assess variance in mental well-being. We will calculate correlation (Spearman’s ρ) between baseline QWB scores and scores at post-treatment (12 weeks) and follow-up (6 months post-treatment). We will estimate differences in mental well-being between the intervention and control groups by calculating mean changes in the QWB from baseline to post-treatment (12 weeks) and from baseline to follow-up (6 months post-treatment), alongside 95% CIs.

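### Harms are defined as SAEs only, so the stated harm report can miss individual non-serious worsening that the trial already measures in both arms

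*Protocol article*

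**What the plan says.** The protocol article, under Harms, gives a closed definition: "We define harms as serious adverse events (SAEs), that is, any expected or unexpected adverse event". An event qualifies whatever its cause, provided that it is fatal, threatens life or leads to admission; suicide attempts and self-harm are named. Ascertainment is stated as follows: "We will assess SAEs through spontaneous reporting by participants to research team members or parent guides and ongoing monitoring by parent guides during intervention delivery".

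Under Intervention and control groups, the reader is told: "Procedures for identifying and responding to participant deterioration or disclosure of risk during the trial are described under Harms". Harms does set out such procedures. They cover staff training, emergency contact, a psychologist's risk assessment for non-acute ideation, referral with exclusion from the trial for parents who need more support, and a guide's own assessment: "If a parent guide identifies signs of serious mental illness (including deterioration) and/or risk of suicide".

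QWB, PHQ-8, GAD-7 and PCL-C are collected in both arms at baseline, 12 weeks and 6 months post-treatment (Clinical and health economic outcomes; Table 3). Their stated analysis is at group level: "For clinical, health economic and process outcomes, we will report means and standard deviations (SDs) for normally distributed continuous variables", medians and IQRs otherwise, and for QWB also the SD, the correlation with baseline and mean changes with 95% CIs. The steering committee reviews recruitment, retention and SAEs (Trial steering committee). Table 2 has no progression criterion on harm.

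**The concern.** The adverse courses that the protocol itself anticipates (deterioration, disclosed ideation, a need for more support than the trial can give) are handled clinically but are not part of the stated harm outcome. A parent can become clearly worse without meeting a seriousness criterion. Group means can hide this when most others improve.

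Three features add weight.

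- **Unequal detection.** Guide monitoring exists only in the intervention arm and only during delivery. Spontaneous reporting is all that is stated for the control arm, and for everyone afterwards.
- **Possible loss of the worst scores.** The text does not say whether parents excluded for needing more support are still assessed. Those who withdraw from the trial are not contacted again, and missing data are not imputed. If excluded parents are treated like withdrawals, some of those who worsened most drop out of the means.
- **No harm criterion.** ENGAGE listed the absence of substantial negative consequences among the criteria it met. Table 2 of the present protocol has no counterpart.

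At stake is the safety input to the decision on a superiority trial. That input could be uninformative about non-serious worsening although the data to describe it are held.

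**Working it through.** The protocol gives no harm rate, harm threshold or harm precision, so there is no figure of its own to reproduce.

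**1. What is managed and what is reported**

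| Event | Managed under Harms | Counted as a harm | Stated by-arm report |
|---|---|---|---|
| Death, life-threatening event, hospitalisation | yes | yes | SAEs go to the steering committee |
| Deterioration without a seriousness criterion | yes | no | none stated |
| Non-acute suicidal ideation | yes | no | none stated |
| Exclusion for needing more support | yes | no | none stated as harm |

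**2. What zero SAEs would mean.** Input: 30 per arm, 60 in total (Sample size). The exact two-sided 95% upper limit after no events is 1 − 0.025^(1/n).

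- n = 30: 1 − 0.025^(1/30) = 11.6%
- n = 60: 1 − 0.025^(1/60) = 6.0%

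**3. How likely zero SAEs is.** P(none) = (1 − p)^n. The document gives no p, so the range below is an assumption.

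| Assumed share with an SAE | None in 30 | None in 60 |
|---|---|---|
| 0.5% | 86% | 74% |
| 1% | 74% | 55% |
| 2% | 55% | 30% |
| 3% | 40% | 16% |
| 5% | 21% | 5% |

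The break-even rate is 1 − 0.5^(1/n): 2.28% for one arm and 1.15% for the whole trial.

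**4. How a mean can hide worsening (invented illustration).** If 3 of 30 worsen by 1 SD and 27 improve by 0.3 SD, the mean change is (27 × 0.3 − 3 × 1)/30 = 5.1/30 = +0.17 SD, although 10% have clearly worsened.

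**5. Whether QWB worsening can be classified from data already planned.** Input: "alpha between 0.93 and 0.94, and high test-retest reliability" (Primary clinical outcome). The reliable-change threshold is 1.96 × √2 × SD_baseline × √(1 − reliability).

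- alpha 0.93: 1.96 × 1.414 × √0.07 = 0.73 baseline SD
- alpha 0.94: 1.96 × 1.414 × √0.06 = 0.68 baseline SD

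No reliability is given for PHQ-8, GAD-7 or PCL-C, so it must be estimated from the trial's baseline data.

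**6. How much natural fluctuation this threshold catches.** Methodological uncertainties says that the correlation of QWB with baseline is unknown. Assume 0.6 to 0.8, equal variances, normal changes and no mean change. The SD of change is √(2(1 − r)).

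- r = 0.6: √0.8 = 0.89 SD; P(fall above 0.73 SD) = P(Z > 0.73/0.89), about 21%
- r = 0.8: √0.4 = 0.63 SD; P(Z > 0.73/0.63), about 12%

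So about 12% to 21% per arm could cross the line with no intervention effect. The count means something only beside the control arm's count.

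**The case against.** The strongest reply is that this is a low-risk feasibility pilot, that the clinical handling of deterioration is in place, and that a deterioration table is ordinary content for an analysis plan. That plan exists but is not shown, and the process evaluation has its own protocol. Much of this stands, and it rules out several stronger readings.

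- A reader might infer that the two sections contradict each other. They do not: one promises procedures to identify and respond, and Harms supplies them. Neither promises a count.
- A reader might infer that deterioration will never be counted. The documents do not show that. The scores would allow it, and the unseen analysis plan or process evaluation may do it.
- A reader might infer that the trial will probably report no harm. That depends on an SAE rate which is not given. Unrelated hospitalisations count, and above about 1.2% over the whole trial at least one SAE is more likely than not.
- A reader might infer that nothing short of admission counts. Death and life-threatening events do. Suicide attempts and self-harm are named, although it is unclear whether they count in their own right or only when a seriousness criterion is met.

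It is also fair that the 11.6% limit would apply to any event not seen in 30 people, that the illustration in step 4 is invented, that reported SDs and IQRs show some spread, and that an alpha-based threshold reflects item error only. Activation counts would favour detection in the intervention arm, which has up to 12 guide sessions (one initial, up to 10 weekly, one relapse prevention).

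What the reply does not remove is the definition itself. The protocol affirmatively equates harms with SAEs and names only SAEs for safety review. A score table in an analysis plan would not by itself change either.

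**Conclusion.** The concern holds in limited form. As written, the harm report covers SAEs only, detection differs between the arms, and no stated rule reports by arm the individual deterioration, non-acute ideation or needs-based exclusions that the same section manages. The report can therefore miss non-serious worsening, and zero SAEs in an arm would leave a true rate of up to 11.6% open.

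This is a reporting gap that should be closed. It is not an error in the clinical procedures and does not invalidate the feasibility aims. The 11.6% limit assumes 30 independent participants with complete ascertainment; spontaneous reporting makes it optimistic. The QWB threshold of 0.68 to 0.73 baseline SD rests on the stated alpha, and the 12% to 21% background rate on an assumed correlation of 0.6 to 0.8.

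**What to change.** Leave the SAE definition and every clinical procedure as they are. Add to Harms a descriptive report by arm, without tests:

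1. **Reliable deterioration** from baseline to 12 weeks and from baseline to 6 months post-treatment. For QWB this is a fall above 1.96 × √2 × baseline SD × √(1 − reliability). For PHQ-8, GAD-7 and PCL-C it is a rise above the same expression, with reliability estimated from the trial's baseline data. Give number/assessed and a 95% CI for each arm.
2. **Each risk-procedure activation and each exclusion for needing more support**, logged and reported by arm and by detection route (assessment call, parent guide, spontaneous contact).

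State two cautions with the tables. Deterioration counts are to be read against the control arm, because the threshold also captures natural fluctuation. Activations are to be read in the knowledge that the intervention arm has more contacts.

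The cost is a short addition to the text, one or two tables and a brief log entry, with no new assessment. Counts will be small and intervals wide. Recruitment began in June 2026, so the log should start promptly and the change should follow the route in Protocol changes. If the analysis plan already contains such a table, a cross-reference from Harms covers item 1, and only the log in item 2 remains to be added.

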### The ENGAGE feasibility trial

Research from the intervention development phase informed the feasibility phase (figure 1) where we conducted the single-arm feasibility trial ENGAGE^30^ to examine procedural, intervention, and methodological uncertainties around the internet-administered version of EJDeR and planned trial procedures for a future evaluation of EJDeR in a superiority randomised controlled trial (RCT). Progression criteria were set a priori, following a GO-AMEND-STOP progression framework.^31^ We enrolled 75 participants (56 identified via the Swedish Childhood Cancer Registry and Swedish Tax Agency’s Population Registry, and a further 19 via other recruitment strategies), of which 72 completed baseline assessments and gained access to EJDeR.

Five progression criteria met GO: (1) 11.0% (56/509) were enrolled of the total potential participant population invited via the Swedish Childhood Cancer Registry and Swedish Tax Agency’s Population Registry, criteria ≥9.0%; (2) 24% (18/75) dropped out of the trial and 23.6% (17/72) dropped out of the intervention, criteria ≤30.0%; (3) 0.01–3.9% of questionnaire items were missing, criteria ≤10.0%; (4) 98.7% (74/75), 84.4% (54/64) and 81.4% (48/59) completed telephone interviews at baseline, post-treatment (12 weeks), and follow-up (6 months post-treatment), respectively, of those remaining in the study at each time point, criteria ≥70.0%; and (5) no substantial negative consequences were reported. Two criteria met AMEND: (1) 65.6% (42/64) and 67.8% (40/59) completed online assessments at post-treatment (12 weeks) and follow-up (6 months post-treatment) respectively of those remaining in the study at each time-point, criterion ≥70.0%); and (2) 47.9% (34/71) completed the minimum treatment dose completion, criterion ≥50.0%.

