### Randomisation: intervention or control group

After assessing eligibility during a structured inclusion interview via telephone (see Data collection methods), eligible participants complete the baseline assessment and are thereafter randomly allocated to the intervention or control group in a 1:1 ratio using block randomisation with a block size of 6. The randomisation sequence is computer-generated to ensure unpredictability and conducted through an online software application (https://www.sealedenvelope.com/) by an individual external to the research team. Following randomisation, the individual external to the research team will notify the research team of the participant’s allocation, after which a research team member will inform the participant of their allocation via SMS. For those allocated to the intervention group, a research team member will provide: (1) workbooks (via post together with an introduction note), (2) access to audio files and video case vignettes (online platform link via SMS), and (3) information about their assigned parent guide (via SMS). The research team will notify the assigned parent guide that they have been allocated a participant and the parent guide will contact the participant within 1 week to introduce themselves and schedule the initial assessment session.

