#### Decision-making about progression to a future superiority RCT

To inform the decision to progress to a future superiority RCT, we will consider the pre-specified progression criteria, feasibility outcomes without progression criteria and findings from the process evaluation.^53^ We will determine, in collaboration with the TSC, whether feasibility outcomes suggest GO, AMEND with modifications or STOP.

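### Active SAE monitoring exists only in the EJDeR arm and ends with delivery, so recorded SAEs will not be comparable by arm; harms are also not a named input to the progression decision.

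*Protocol article*

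**What the plan says.** The Harms section of the protocol article sets a wide scope: "We define harms as serious adverse events (SAEs), that is, any expected or unexpected adverse event, related, possibly related or unrelated" to the intervention or the trial, if it is fatal, life-threatening or leads to hospital care, with suicide attempts and self-harm included. Events in controls are therefore in scope. The means of detection are "spontaneous reporting by participants to research team members or parent guides and ongoing monitoring by parent guides during intervention delivery".

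Guides belong to one arm. Under Randomisation, "For those allocated to the intervention group, a research team member will provide" the workbooks, the online access and the details of the assigned guide. Under Telephone guidance, in the first week "the parent guide schedules an initial assessment session (≈45 min) with the parent"; after that "the parent guide provides up to 10 weekly telephone" check-ins, and a relapse prevention session follows in week 12. Both arms receive telephone assessments at 12 weeks and at 6 months post-treatment. Table 3 lists the instruments for those calls and shows no SAE item.

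On progression, Table 2 has four criteria: proportion of those invited who are randomised, questionnaire completion, missing responses and minimum dose. The decision section states that "we will consider the pre-specified progression criteria, feasibility outcomes without progression criteria and findings from the process evaluation". In the predecessor trial, that "no substantial negative consequences were reported" was listed among the criteria that met GO. The Trial steering committee section says this committee reviews SAEs and advises the research team.

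**The concern.** A count of SAEs reflects how often events occur and how hard one looks for them. Here the second factor differs by arm by design. A guide who speaks to a participant most weeks will hear of an admission or a self-harm episode that a control might never think to telephone in. With equal true risk, the EJDeR arm would tend to show more SAEs because it is watched more closely. Some control events, and some events in either arm after delivery ends, could go unrecorded.

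Two things are at stake. There is no independent data monitoring committee, and the steering committee is asked to advise on safety, so its information should be even across arms. Also, the second objective is to test study procedures for a superiority RCT with the same comparison. A harms procedure that works alike in both arms is one of those procedures, and as written it would not be tried out.

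**Working it through.** The protocol states no SAE rate, capture rate or harms threshold, so there is no figure to reproduce. The check is a count of contacts, followed by an illustration.

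**1. Scheduled contacts after randomisation** (Telephone guidance; Minimum treatment dose; Post-randomisation assessments)

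| | EJDeR, maximum | EJDeR, minimum dose | Control |
|---|---|---|---|
| Initial guide session | 1 | 1 | 0 |
| Weekly check-ins | 10 | 4 | 0 |
| Relapse prevention session | 1 | 0 | 0 |
| Assessment calls | 2 | 2 | 2 |
| Total | 14 | 7 | 2 |

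Up to the 12-week call, guide contacts are at most 1 + 10 + 1 = 12 in EJDeR and 0 in control.

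**2. Effect of unequal capture (illustration only).** Let n = 30 per arm (Sample size section), with the same true risk p in both arms and capture probabilities c_E and c_C. Expected recorded participants with an SAE are n·p·c_E and n·p·c_C, so the spurious ratio is c_E/c_C whatever p is. With c_E = 0.90 assumed:

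- c_C = 0.80: 0.90/0.80 = 1.125
- c_C = 0.60: 0.90/0.60 = 1.5
- c_C = 0.40: 0.90/0.40 = 2.25

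**3. In counts.** Assume p = 5% and c_C = 0.50. Expected counts are 30 × 0.05 × 0.90 = 1.35 in EJDeR and 30 × 0.05 × 0.50 = 0.75 in control. The chance that control records none is (1 − 0.05 × 0.50)^30 = 0.975^30 = 0.47. With 90% capture in both arms it would be (1 − 0.045)^30 = 0.25. From the exact binomial distributions, EJDeR shows more SAEs than control with probability 0.51, and control shows more with probability 0.21. Under equal 90% capture both probabilities are 0.37.

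**4. Artefact against chance.** Assume p = 10% and c_C = 0.40. Expected counts are 30 × 0.10 × 0.90 = 2.7 and 30 × 0.10 × 0.40 = 1.2, a difference of 1.5. The standard deviation of the difference is √(30 × 0.09 × 0.91 + 30 × 0.04 × 0.96) = √3.61 = 1.9. Even at this low control capture the artefact is smaller than chance variation.

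**5. What zero events would show.** With full capture, 0 of 30 leaves a one-sided 95% upper limit of 1 − 0.05^(1/30) = 9.5%. Incomplete capture makes a control count of zero less informative still.

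**The case against.** The strongest reply is that this is a small descriptive pilot of an intervention the protocol calls low-risk, with no planned comparison of SAEs between arms. The Blinding section says the trial is not built for inference on group differences, and the Statistical methods section plans no SAE test. Controls are not unobserved: they can report to the research team at any time, and staff who collect data are trained to recognise serious mental illness and suicide risk. The structured telephone script mentioned under Blinding is not shown and may ask more than Table 3 lists. Fourteen contacts is a ceiling. Most of this stands and limits the weight of the point. It does not remove it, because the Harms section itself states the SAE routes and the only active one is confined to one arm.

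Three stronger readings are tempting and are not supported:

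- **Harms play no part in the progression decision.** The decision is taken with the steering committee, which reviews SAEs, so they may be weighed informally. The text supports only that harms have no criterion and are not a named input. Not carrying over ENGAGE's harms criterion is a choice, not a contradiction.
- **Nobody is monitored after week 12.** The section on interim analyses says SAEs are monitored throughout the trial, and trained assessors call both arms at 6 months. Only guide monitoring ends.
- **EJDeR will appear 2.25 times as harmful.** That figure depends wholly on assumed capture rates; another assumption in the same range gives 1.1.

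**Conclusion.** The point holds in a limited form and is worth an amendment. SAE ascertainment is unequal by design: one arm has an active route with up to 12 contacts before the 12-week call, and the other has spontaneous reporting alone over that period. A table of recorded SAEs by arm could not be read as a comparison, and the harms procedure for the future RCT would go untested in balanced form. The likely direction is more recorded SAEs in EJDeR.

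The size is unknown. The spurious ratio of about 1.1 to 2.25 assumes equal true risk, 90% capture in EJDeR and 80% to 40% in controls, none of which the documents supply. The four criteria in Table 2 are unaffected, and no planned analysis is invalidated.

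**What to change.** - **Harms section and telephone scripts:** add the same scripted SAE question to the 12-week and 6-month calls in both arms. Use the protocol's own SAE definition and cover the time since randomisation or the last assessment. If the script already asks this, say so in the Harms section.
- **Recording and reporting:** record the source of each SAE (solicited at a call, guide-reported, spontaneous) and report descriptively by arm and source, without a test.
- **Resource Use Questionnaire:** use it only as a supplementary prompt. As described it covers "emergency department visits and other healthcare services" but does not name hospital admissions, so it cannot replace the direct question.
- **Decision-making section:** name SAEs among the inputs to GO-AMEND-STOP.

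The cost is about a minute in a call of about 30 minutes, some further reports through the existing risk pathway, and a minor amendment by the route under Protocol changes. Recruitment opened in June 2026, so some 12-week calls may precede the change. For those participants, the 6-month question should reach back to randomisation. Two limits remain. Participants who miss the calls give no solicited data: at the 70% completion threshold for all questionnaires, up to 0.30 × 60 = 18 could lack at least one complete assessment. The assessors are also unblinded. The solicited counts will therefore be more even across arms, but not free of bias. No clinical rule changes.
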